**Figure 1 Fig1:**
[figure not shown]
**Illustration of spinal stiffness assessment tests.** Skin marks over bony landmarks of the T11-L5 spinous processes and posterior superior iliac spine **(A)**, palpatory stiffness assessment **(B)**, stiffness assessment with a hand-held device **(C)**; and stiffness assessment with an automated device **(D)**.

The automated stiffness test consists of 1) a height-adjustable treatment table equipped with safety switches to allow either the participant or examiner to immediately lower the table thereby withdrawing from the automated stiffness device; 2) an automated stiffness device that extends and applies a designated force; and 3) a computer system to program device movement based on displacement/force data sent from the device in real-time using a custom-written program in LabVIEW with a sampling rate at 200Hz (Version 8, National Instruments Corp., Austin, TX)
[23, 58, 59]. The automated stiffness device is positioned over the spinous process nearest the most concave point of the lumbar curve while in the prone position, typically corresponding with the L3 spinous process. When the lumbar spine is not concave in shape (e.g. flat or convex lumbar spine) or the L2 or L4 level appears to be at similar height as L3, the automated stiffness device is placed over the L3 spinous process. Participants are instructed to lay prone, inhale then exhale normally, and hold their breath at the end of exhalation for approximately 10 seconds during which the automated stiffness test is performed. During the test, the actuator on the automated device advances at a rate of 2.5 mm per second. After reaching a preload force of 5 N on the target spinous process, the actuator holds the preload for one second before advancing further and applying a maximum load of 60 N. The maximum load is maintained for one second before the actuator retracts. To decrease participant’s burden in holding the breath, the initial position of the actuator is placed as close as possible to the target spinous process as long as the participants can breathe normally without pushing against the actuator. The procedure is conducted three times during each assessment with a testing trial performed prior to data collection to orient the participant to the procedure and to determine safety. The average stiffness of the three trials is used for analysis. Figure 
1D demonstrates the setup for the automated stiffness measurement.

*Data reduction*: For all three stiffness measurement tests, force and displacement data are acquired simultaneously. Data acquired from the hand palpation and hand-held stiffness tests are exported into a custom-written MATLAB program (MathWorks Inc., Natick, MA) and the graphs of displacement against force are plotted. The user identifies the points corresponding to 10 N and 60 N and the software computes the slope of the curve within the region using linear regression. For the automated stiffness test, the LabVIEW program is used to compute stiffness using the same algorithm as that of the MATLAB program. It is worth noting that spinal stiffness obtained *in vivo* in the current study is different from the inter-segmental stiffness typically obtained in specimen studies. To distinguish between them, the term global stiffness was suggested to describe the stiffness measurement over a region of the spine containing several segments
[60]. Consultation with DCs performing treatments in this study revealed that relative perceived stiffness as opposed to the absolute stiffness of a given spinal segment provides the most useful clinical information. Therefore, to be consistent with the clinical interpretation utilized by study DCs the global stiffness variation (GSV) is calculated as:

where gs_i_ is the global stiffness measured at the lumbar spine and *i* = 1,2,…,5.

To account for the between-subject variation in the global stiffness measurement (e.g. a participant may have an overall stiffer or more flexible lumbar spine), the normalized *GSV* (*nGSV*) is calculated as:

Both *GSV* and *nGSV* are obtained from the palpatory and hand-held stiffness tests and will be used in data analysis.

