1A). During the hand palpation assessment, the participants lie face down on a custom-made chiropractic treatment table with force plates (Model 4060-NC, Bertec Inc., Columbus, OH) embedded under the cushions that support the thoracic and pelvic regions and acquire the palpatory force transmitted through the participant. The clinician applies a gentle anteriorly directed force consistent with the level typically used during examination to the vertebral levels L1 to L5. An infrared smart marker (Optotrak 3020/Certus hybrid system, Northern Digital Inc., Waterloo, Ontario, Canada) is placed on the clinician’s palpatory hand to simultaneously acquire displacement. The sampling rate for the Optotrak system is set at 100 Hz while the sampling rate for the force plates is set at 1000 Hz. No specific instruction is given to participants in terms of their breathing during the test. Figure 1B demonstrates the setup for the palpatory stiffness measurement.

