The hand-held stiffness device consists of a force transducer (Model # LC201-50, Omegadyne Inc., Sunbury, OH) and infrared smart markers for accurate force and displacement measurement. The assessment is performed with the participant lying prone on the treatment table. The examiner assesses tolerance of participants by pressing gradually up to a maximum of 80 N with the stiffness device in an anterior direction over the pre-marked spinous process of each lumbar vertebra from L1-L5. Participants inform the examiner if the pressure causes discomfort. When the maximum pressure of 80 N is reached an audible tone sounds as feedback to the examiner to stop compressing and withdraw the device. If pressure from the stiffness device causes discomfort, the test is reapplied more slowly and the participant indicates the level of pressure causing discomfort. If the tolerance test does not cause discomfort with 80 N of pressure at any vertebral level, the subsequent stiffness tests are conducted with a maximum pressure of 80 N. If the participant indicates discomfort during the tolerance test, the subsequent stiffness test is conducted at all vertebral levels using a maximum force value 10 N lower than the lowest value causing discomfort at any vertebral level during the tolerance test. If tolerance to the hand-held stiffness device is less than 60 N at any vertebral level, the hand-held stiffness test, as well as the automated stiffness test, is not performed. Both force and displacement are recorded using a Motion Monitor data acquisition workstation (Innovative Sport Training, Chicago, IL) at a sampling rate of 1000 Hz. The stiffness measures are performed by pressing anteriorly over each lumbar spinous process for 5 cycles at a rate of approximately 1 repetition per second. The participants are instructed to make a deep breath in, a deep breath out, and then inhale half way and hold their breath during which the test is performed. The average stiffness obtained over the last 4 cycles is used for analysis. Figure 
1C demonstrates the setup for the hand-held stiffness measurement.

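### As written, the hand-held stiffness test can stop at 50 to just under 60 N, but the primary stiffness measure is a slope that runs to 60 N

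*Protocol article*

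**What the plan says.** All the rules are in the protocol article, under Primary outcome measures, Posterior-anterior stiffness of the lumbar spine. That section names the hand-held device as the primary way of measuring stiffness.

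- **Tolerance test.** The examiner assesses tolerance at L1 to L5 by "pressing gradually up to a maximum of 80 N with the stiffness device". A participant who feels discomfort reports the pressure at which it occurs.
- **Cap for the test proper.** Without discomfort, "the subsequent stiffness tests are conducted with a maximum pressure of 80 N". With discomfort, "the subsequent stiffness test is conducted at all vertebral levels using a maximum force value 10 N lower than the lowest value causing discomfort".
- **Omission rule.** "If tolerance to the hand-held stiffness device is less than 60 N at any vertebral level", neither the hand-held nor the automated test is done.
- **Automated test.** "the actuator holds the preload for one second before advancing further and applying a maximum load of 60 N".
- **Definition of stiffness (Data reduction paragraph).** "The user identifies the points corresponding to 10 N and 60 N and the software computes the slope of the curve within the region". The automated device uses the same algorithm. GSV and nGSV are then formed from the five level-specific values of the palpatory and hand-held tests.

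The section gives no other slope window, and no handling rule for a test whose maximum is below 60 N.

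**The concern.** The omission rule and the cap are both expressed in newtons, but they seem to refer to different quantities. The first is compared with tolerance, and the second is the discomfort force less 10 N. If tolerance is the discomfort force, some participants pass the omission rule and are then tested below the upper end of the slope window. Their primary stiffness value is either missing or taken over a shorter range that the user picks without a written rule.

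These are the most tender of the participants who are still tested. Specific Aim 1 seeks preliminary estimates of variability and effect size for the association of stiffness with pain and function. A measure whose definition changes with tenderness is awkward for that purpose, because tenderness is plausibly related to the pain outcome.

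**Working it through.** **Inputs, all from the stiffness section.** Tolerance test ceiling 80 N; cap D − 10 N, where D is the lowest force causing discomfort, otherwise 80 N; test omitted if tolerance is below 60 N; slope window 10 to 60 N; automated load 60 N. The plan states no figure to reproduce. The check compares thresholds.

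**Step 1. When does the curve reach 60 N?** It does so if D − 10 ≥ 60, that is D ≥ 70 N, or if there is no discomfort.

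**Step 2. Compare with the omission rule under two readings of tolerance.**

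| D (N) | Cap (N) | Performed if tolerance = D | Performed if tolerance = D − 10 | 60 N reached |
|---|---|---|---|---|
| 59 | 49 | no | no | no |
| 60 | 50 | yes | no | no |
| 65 | 55 | yes | no | no |
| 69 | 59 | yes | no | no |
| 70 | 60 | yes | yes | yes |
| 80 | 70 | yes | yes | yes |
| none | 80 | yes | yes | yes |

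On the first reading the gap is 60 ≤ D < 70 N. The curve then covers (50 − 10)/50 = 80% to just under 100% of the window. The cap applies at every level, so all five level values lack the 60 N point, and GSV and nGSV are built on them. On the second reading there is no gap.

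**Step 3. The automated test.** On the first reading, participants in the gap are not excluded from it. It loads to 60 N, above their own cap of 50 to just under 60 N.

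**Step 4. Size, if the slope were fitted only up to the cap.** The document gives no curve shape, so one is assumed: F = c·d^p, with p from 1.2 to 2. The table gives the least-squares slope from 10 N to the cap, divided by the slope from 10 to 60 N.

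| p | Cap 50 N | Cap 55 N | Cap 59 N |
|---|---|---|---|
| 1.2 | 0.977 | 0.989 | 0.998 |
| 1.5 | 0.956 | 0.979 | 0.996 |
| 2.0 | 0.938 | 0.970 | 0.994 |

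The row for p = 2 can be checked by hand. With points evenly spaced in displacement, the fitted slope is proportional to √10 + √cap, so the 50 N ratio is (3.162 + 7.071)/(3.162 + 7.746) = 0.938. The shortfall is therefore about 2–6% at 50 N, 1–3% at 55 N and under 1% at 59 N.

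A second assumed shape, with tangent stiffness rising linearly with force by 0 to 100% between 10 and 60 N, gives 0–5.9%, 0–2.9% and 0–0.6%. A straight curve gives no shortfall.

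**Step 5. Number affected.** The document gives no distribution of discomfort forces, so the count cannot be derived. As an illustration only, an assumed share of 5–15% of the planned 80 participants would be 4 to 12 people.

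**The case against.** The strongest reply is that everything turns on one undefined word. The omission threshold, the automated load and the upper end of the slope are all 60 N, which suggests that the authors meant them to match. If tolerance means the force at which a participant can be tested, they do match. This is a fair account of a possible intention. However, the text describes assessing tolerance by pressing until discomfort and recording that pressure, and it never says that the threshold applies to the reduced value. Two analysts could treat the same participant differently.

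The second reply concerns size, and most of it stands. The 6% figure needs both the steepest assumed curve and D of exactly 60 N. The article itself quotes a reliability of 0.79 for the hand-held device, so a shift of a few per cent in an unknown minority is unlikely to dominate. In the assumed model the ratio does not depend on c. If p is equal across levels, all five values shrink by one factor, and nGSV would be unchanged if it is scale-free. Its formula is not visible here, so that is an assumption. It also does not help if the value is treated as missing.

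A reader might go further and infer that the stiffness–outcome association is biased. The documents do not support that: the affected share is unknown, no effect on any association has been calculated, and the aim is preliminary estimation. Nor do they show that palpation misses 60 N. They describe a force that "applies a gentle anteriorly directed force consistent with the level typically used during examination" but give no figure for it. Leaving out participants below 60 N is a stated rule and not in itself an error.

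**Conclusion.** The point holds as a conflict between stated rules for the primary stiffness measure. It is more than a detail left to an analysis plan, because the article itself fixes the cap, the omission threshold, the automated load and the slope window. On the ordinary reading, participants with discomfort at 60 to just under 70 N have a performed hand-held test but no slope as defined, and they remain eligible for a 60 N automated load above their cap. The conclusion rests on tolerance meaning the discomfort force and disappears if it means the reduced maximum.

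The numerical effect of a shortened window is probably modest: at most about 6% on the assumed curves, and less over most of the gap. What makes it worth correcting is that it depends on tenderness and that no rule says what the analyst should do.

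**What to change.** Reconcile four items in the stiffness section: what tolerance refers to, the cap of 10 N below discomfort, the 60 N automated load, and the 10–60 N slope window. Which force rule is right is for the investigators to state and is not proposed here. If tolerance was applied as the reduced maximum, a sentence saying so closes the point.

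If tests capped below 60 N were performed, compute hand-held stiffness for all tested participants over one common force window that every performed hand-held test reaches. On the discomfort-force reading, the arithmetic above means that its upper end cannot exceed 50 N. Report the 10–60 N slope alongside it for participants who reached 60 N, and form GSV and nGSV from the common-window values.

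The cost is a wording correction and a re-run of the existing reduction program on stored curves. No new data are needed. The narrower window makes the slope slightly noisier for everyone.

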#### Flexion-relaxation phenomenon

Surface EMG measurements of lumbar paraspinal muscle activity for FRP analysis in this study were initially taken with a system using Ag/AgCl electrodes built into a plastic enclosure along with a solid state preamplifier (Therapeutics Unlimited model 544, Iowa City, IA – no longer in business). Motion data were initially taken with an electronic goniometer (SG150B, Biometrics Ltd, Newport, UK) that was synchronized with the EMG system. After the first 30 participants, both measurement systems were replaced with a wireless EMG system with integrated accelerometers to provide motion data (Delsys Inc. Trigno Wireless System, Natick, MA). The major difference between the two EMG systems is that the original system had fixed-distance electrodes, whereas the current Delsys system uses two separate electrodes. The EMG and motion data are recorded using the Motion Monitor workstation with a sampling rate of 1000 Hz.

FRP measurements take place pre and post treatment during TV1, TV5, and TV12. The skin over the lumbar paraspinal muscles is prepared by vigorously rubbing the skin with an alcohol wipe. The participant, seated on a stool, leans forward while disposable, self-adhesive, pre-gelled surface EMG Ag/AgCl snap electrodes (Disposable ECG electrode white foam type, 36 mm in diameter, AMBU Inc., Copenhagen, Denmark) are placed on the skin over the mid-lumbar paraspinal muscles (Figure 
2). Specifically the electrodes are placed with one above and one below the L3 level on each side with approximately 1 cm vertical distance between the edges of the electrodes in a semi-flexed position such that when the participant sits erect, the electrodes do not touch. Because the electrodes are removed to enable HVLA-SM, the outline of each electrode is drawn with a skin marking pen so new ones can be placed in the same location for the post treatment measurements.

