#### Posterior-anterior stiffness of the lumbar spine

Lumbar spine stiffness is assessed sequentially with three approaches using hand palpation, a hand-held instrumented device, and an automated device, respectively. The hand-held instrument approach is the primary measure as it has been validated by our study team and demonstrated good reliability (0.79)
[56, 57]. The same set-up allows us to implement hand palpation in a manner that mimics spinal stiffness assessments in clinical practice and will allow us to explore the association between stiffness as measured by palpation versus the hand-held instrument. Because the hand palpation approach was thought to be less intrusive, it is tested before the hand-held approach in the trial. As we finalized the protocol for study launch, a study using an automated stiffness assessment method with high within- and between-day reliabilities (0.99 and 0.98) was published and suggests that spinal stiffness may have important clinical implications
[23]. We contacted the authors who loaned us the equipment for use as an added stiffness measure. However, due to the study timeline, and technical and training requirements, the automated stiffness procedure was not implemented until the clinical trial enrolled 20 participants.

During stiffness assessments, participants lie prone while study clinicians mark the skin with a sterile surgical marking pen at the following locations: posterior superior iliac spines, spinous processes the seventh cervical vertebra (C7), the eleventh thoracic vertebra (T11) to the fifth lumbar vertebra (L5), interspinous spaces from T10 to the first level of sacrum (S1), and the most concave lumbar segment while lying prone (Figure 

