**Figure 2 Fig2:**
[figure not shown]
**Illustration of EMG electrode placement (A) and example EMG and motion signals (B).** Root-mean-square (RMS) EMG data and motion data are scaled according to the maximum of RMS EMG data **(B)**. B contains 3 cycles of flexion (B1), holding in position while fully flexed (B2), and extension (B3).

Participants are instructed to place their feet shoulder width apart with their arms hanging loosely at their side. Keeping their knees straight, they bend forward as far as they can and hold that position for 3 seconds, then return to the upright standing position. Participants perform this movement once as practice and to allow research personnel to ensure proper functioning of the system. The participant then performs the procedure 3 times in a continuous manner while the EMG and motion data are collected.

*Data reduction*: In order to quantify the degree to which the FRP is present, two different forms of a flexion-relaxation ratio (FRR) are used
[31, 32]. One is calculated by dividing the maximum root mean square (RMS) EMG activity level during flexion (while bending forward) by the lowest mean EMG activity as measured over a one second interval during the fully flexed phase. Another FRR is similarly calculated by dividing the maximum RMS EMG activity level during extension (while returning to standing erect) by the same minimum. The beginning and end of the fully flexed phase for each cycle are determined from the plot of the motion data. A macro written in Visual Basic for Applications, within Microsoft Excel (Microsoft Corp., Redmond, WA), is used to identify the specific regions of the data plots. These are regions of full flexion, the regions in which the trunk is flexing forward, and the regions in which the trunk is extending while returning to the upright position. The macro allows the user to adjust the limits of the various regions of the plot in order to exclude occasional spurious spikes in the RMS EMG data.

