#### Sample size

A minimum of 80 participants will be enrolled in the current study. The sample size should be sufficient to obtain preliminary estimates of variability and effect size through our planned data analysis, taking into consideration the possibility of dropouts and technical issues that may occur given the rigor and complexity of this study protocol.

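### The EMG and motion systems used for flexion-relaxation changed after participant 30, and the stated Aim 1 model has no term to keep a system difference out of its variance and association estimates

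*Protocol article*

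**What the plan says.** Under Flexion-relaxation phenomenon, the article says that "After the first 30 participants, both measurement systems were replaced with a wireless EMG system with integrated accelerometers to provide motion data". It names the main EMG difference: "the original system had fixed-distance electrodes, whereas the current Delsys system uses two separate electrodes". The motion sensor changed too: "Motion data were initially taken with an electronic goniometer", and accelerometers took over later. No side-by-side recording, calibration or agreement study between the two set-ups is described.

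The data-reduction paragraph of the same section makes the FRR depend on both systems. The flexion form is obtained by "dividing the maximum root mean square (RMS) EMG activity level during flexion (while bending forward) by the lowest mean EMG activity", where the denominator is the "lowest mean EMG activity as measured over a one second interval during the fully flexed phase". The extension form uses the same denominator. The window comes from the other sensor: "The beginning and end of the fully flexed phase for each cycle are determined from the plot of the motion data".

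Under Statistical analysis, Specific Aim 1 summarises the physiological measures with a hierarchical linear regression containing a participant random effect, and then relates them to the patient-centered outcomes. No term for recording system is named. The alternative models promised at the end of that section test assumptions about consistency.

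The Sample size section gives the purpose of the data: "The sample size should be sufficient to obtain preliminary estimates of variability and effect size through our planned data analysis".

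A separate equipment matter appears under Posterior-anterior stiffness of the lumbar spine: "the automated stiffness procedure was not implemented until the clinical trial enrolled 20 participants".

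**The concern.** The FRR is one of the two physiological measures that Aim 1 is about, and the study's product is a set of planning figures: how much the FRR varies and how strongly it relates to outcome. About three eighths of the planned participants have it recorded with one combination of electrodes and motion sensor, and the rest with another.

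If the two set-ups give different average ratios, a model with only a participant random effect has one place to put the difference, namely between participants. Participant variance is then too large. Because the added spread is unrelated to a participant's pain or disability, the correlation with outcome is diluted. A later trial planned on these figures would inherit both errors. The switch also coincides with calendar time, so without a system term a change of equipment cannot be told apart from a drift in who was enrolled.

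**Working it through.** **Inputs from the article.** System change after 30 participants; minimum enrolment 80; accrual about 4 per month; treatment about 6 weeks. The accrual figure reproduces: 80 / 20 months = 4 per month. The figure of 80 itself cannot be reproduced, because no statistical inputs are given for it.

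**Assumptions.** d is the mean FRR difference between systems, in units of the within-system SD. The article gives no value, so a range is shown. The true within-system correlation is taken as r = 0.30, and the outcome is taken not to drift between the two enrolment periods.

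**Formulas.** The share on the old system is p = 30/80 = 0.375, so p(1 − p) = 0.375 × 0.625 = 0.234. The pooled variance is the within-system variance × [1 + p(1 − p)d²]. The pooled correlation is r / √[1 + p(1 − p)d²].

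| d (assumed) | p(1 − p)d² | Variance factor | Correlation factor | r = 0.30 becomes |
|---|---|---|---|---|
| 0.2 | 0.009 | 1.009 | 0.995 | 0.299 |
| 0.5 | 0.059 | 1.059 | 0.972 | 0.292 |
| 0.8 | 0.150 | 1.150 | 0.933 | 0.280 |
| 1.0 | 0.234 | 1.234 | 0.900 | 0.270 |
| 1.5 | 0.527 | 1.527 | 0.809 | 0.243 |
| 2.0 | 0.938 | 1.938 | 0.718 | 0.216 |

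**Where the extra variance goes.** It falls on the participant component. With an assumed intraclass correlation of 0.70 and d = 1, the between-participant part rises from 0.70 to 0.70 + 0.234 = 0.934, and the intraclass correlation to 0.934 / (0.934 + 0.30) = 0.757. At d = 0.5 it is 0.717.

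**Effect of a system term.** In 20,000 simulated data sets of 30 + 50 participants with true r = 0.30, the mean correlation without a system term was 0.298, 0.289, 0.270 and 0.241 for d = 0, 0.5, 1.0 and 1.5. With system adjusted for, it was 0.298, 0.298, 0.301 and 0.299.

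**Consequence for a later trial.** By the Fisher z formula, n = [(1.96 + 0.84) / atanh(r)]² + 3, with two-sided 5% and 80% power both assumed. This gives 85 participants for r = 0.30, 91 at d = 0.5, 106 at d = 1.0 and 131 at d = 1.5.

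**Change over visits.** For a participant measured on one system throughout, an additive shift appears in every assessment and cancels from the change. At 4 per month over 6 weeks, about 4 × 6 / (52/12) = 5.5 participants would be under treatment at any moment. The article does not say that any of them changed system mid-course.

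**The case against.** The strongest reply is that the article never says the data from the two systems are combined without adjustment. It names a model class and a random effect, lists no fixed covariates at all, and condenses a fuller document. A system covariate could sit in an analysis plan that is not shown. This stands as far as wording goes: pooling is inferred from the stated model. But the article goes beyond silence. It reports the switch as already made, then sets out a model, a rule for choosing the next model and a set of sensitivity analyses, and none of them takes up the switch.

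Second, the FRR is a ratio within one test, so a pure difference in amplifier gain cancels. The user can also adjust the window limits. Both points are right and make a small d plausible. They do not make it zero: electrode spacing, any difference in baseline noise and the motion-defined window need not cancel. The protocol's own account is that patients with low back pain often fail to relax fully, so the denominator should not be assumed near-silent.

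Third, a reader might infer more than the documents support:

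- **Carry-over from the automated stiffness test.** It precedes flexion-relaxation in the sequence and began late, but nothing shows that it alters the FRR. Participants already undergo palpation and, if they tolerate it, repeated hand-held loading at five levels. Its late start is a matter of missing stiffness data.
- **A ceiling of 50 or 60 on the usable sample.** The Sample size section sets 80 as a minimum, and adjusting for system discards nobody.
- **False change over visits.** The switch is described by participant, so this rests on speculation about a handful of people.

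**Conclusion.** The point holds as a weakness of the stated Aim 1 model for flexion-relaxation. A known change of both recording systems is left unmodelled, and any mean difference would inflate between-participant FRR variance and attenuate the cross-sectional and predictive associations.

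Its size is conditional on a shift that the article does not report. It is negligible at 0.2 SD, modest at 0.5 SD and material from roughly 0.8 to 1 SD. The documents do not show that the estimates are in fact contaminated. The attenuation figures also assume no link between outcome and enrolment period; with such a link the bias could go either way.

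The problem does not extend to the stiffness measures, including the primary hand-held one, nor, for an additive shift, to within-participant change in anyone kept on one system. It is worth correcting because the remedy is nearly free and the affected figures are what the study is meant to deliver.

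**What to change.** 1. Record which EMG and motion system was used at each flexion-relaxation assessment, so that any participant measured on both can be identified.
2. Add system (old or new) as a fixed effect in every flexion-relaxation model, including those that relate the FRR to outcome.
3. Report FRR variability and the FRR–outcome association for each system, together with the system-adjusted overall estimate.
4. State in the Sample size section that automated stiffness data exist only for participants enrolled after the first 20.

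A covariate for whether the automated test was done should not be added. Participants who tolerate less than 60 N do not receive that test, so the indicator would also carry pain tolerance. Analysing log(FRR) is reasonable as a sensitivity analysis, but it turns only a purely multiplicative system effect into an offset and does not replace the system term.

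The cost is about one degree of freedom and slightly wider intervals. The by-system estimates will be imprecise at about 30 and 50 participants and should be presented as descriptive. No new measurements are needed.
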